### Study Procedure

All participants will be recruited from the abovementioned universities via advertisements on online bulletin boards, campus newspapers, and posters. Interested students who contact the researchers via email will be provided with further information related to the study and will be given time to consider their participation. If interested, they will be screened using Google forms (developed by the authors for this study) for eligibility using the Japanese version of the CES-D [30]. The cutoff score of CES-D was verified in Japanese samples [30]. If the score is 16-24, the researcher will continue with the eligibility interview to confirm that all other criteria are met. At the end of the interview, written consent will be obtained. Those who score less than 15 or above 25 will be excluded from the trial but will be provided with free access to SPARX, according to the needs of the participant. Those whose score is 25 or more, indicating severe depressive symptoms [31,32], will be provided with information about available mental health care services.

For participants in the treatment condition, SPARX will be delivered on their mobile phone or tablet device. They will be asked to play the SPARX program weekly at a designated university location (eg, a vacant laboratory or conference room) with one of the researchers (or a research assistant) present in another room (eg, a neighboring laboratory) for the purpose of checking SPARX use and being available to answer any questions from the participant. Each weekly session with SPARX is expected to take about 30 min.

Participants in the wait-list condition group will receive access to SPARX after a 1-month follow-up assessment of the treatment condition group. They will be asked to fill out assessments at the same time as the assessments of the treatment condition group at experimental laboratories, in conference rooms at each university, or on online Google forms. They will not be granted access to SPARX until all assessments have been completed.

To address potential issues of contamination, we forbid participants from talking about any theme of SPARX, such as the use of SPARX and any impressions of this study, during trial participation because other students in their university campus are participating in the current trial.

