### Measures

The primary outcome (Japanese version of PHQ-9) will be measured at baseline (T1), weekly throughout the interventions (T2-T7), at postassessment 1 week after the 7 intervention weeks (T8), and at 1-month follow-up (T9). Other assessments will be conducted at preassessment (T1), postassessment (T8), and 1-month follow-up (T9). Table 1 shows the schedule of assessments at various time points. At baseline (T1), demographics data will be collected, including gender, age, major in university, year of study, residence status; presence or absence of visits to psychiatric and counseling services; and presence or absence of the use of a gamified psychological program.

**Table 1 table1:** Overview of measurements.

Outcome	Scale	T1^a^	T2-T7^b^	T8^c^	T9^d^
Demographics	Developed by the authors	✓			
Depressive symptoms	PHQ-9^e^	✓	✓	✓	✓
Satisfaction with life	SWLS^f^	✓		✓	✓
Negative and positive moods	POMS-2^g^	✓		✓	✓
Social functions	EQ-5D^h^	✓		✓	✓
Rumination	RSS^i^	✓		✓	✓
Coping	Brief COPE^j^	✓		✓	✓
Stressor	DLSS^k^	✓		✓	✓
Satisfaction and acceptability	Developed by the authors				✓

^a^T1: baseline assessment (preassessment).

^b^T2-T7: assessment at each level.

^c^T8: assessment 1 week after the program.

^d^T9: assessment at 1-month follow-up.

^e^PHQ-9: Japanese version of Patient Health Questionnaire-9.

^f^SWLS: Satisfaction With Life Scale.

^g^POMS-2: Profile of Mood Scale, second edition.

^h^EQ-5D: Japanese EuroQol instrument.

^i^RSS: Japanese version of the Ruminative Responses Scale.

^j^Brief COPE: Brief Coping Orientation to Problem Experienced inventory.

^k^DLSS: Daily Life Stress Scale for undergraduates.

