##### The Daily Life Stress Scale for Undergraduates (DLSS)

This is a self-reported questionnaire for assessing daily life stressors for undergraduates [48]. The questionnaire consists of 23 items evaluated on a 5-point Likert-type scale (1-5). Higher scores indicate more frequent stressors. Its reliability and validity for a Japanese population have been reported [48].

The final secondary outcome will be a measure of the satisfaction and acceptability of the intervention. All participants will be asked to rate four statements related to the perceived helpfulness, satisfaction with use, and the depth of understanding of the content of SPARX on an 11-point scale (0-10). Participants will also be able to write free text comments. The following questions will be asked: “How useful was this program for you [0 (not at all), 10 (very useful)]? Specifically, which components of this program were useful for you (write free text comments)?” “How satisfied are you with this program [0 (not at all), 10 (very satisfied)]?” “Please tell me about the pros and cons of this program (write free text comments)?” “How fun was this program for you [0 (not at all), 10 (very fun)]?” These items were developed specifically for the current trial.

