### Statistical Analyses

The analysis for primary outcome measures will be conducted using a linear mixed model (LMM). The LMM approach was selected because of its strength in accommodating missing data and its ability to incorporate random effects into analyses. In these analyses, the dependent variable is the PHQ-9 score, and the independent variables are assignment (treatment condition, wait-list condition) and time [preassessment (T1), each session assessment (T2-T7), post-assessment (T8), and follow-up assessment (T9)], with interaction of the assignment and time as fixed-effect variables and participants as a random-effects variable. Secondary outcomes (outcome measures, process measures, and evaluation of the program) will be analyzed in the same way as the primary outcome. Subgroup analyses are not planned. For all analyses, *P*<.05 will be inferred as statistically significant. Up-to-date versions of R software (R Foundation for Statistical Computing, Vienna, Austria) will be used to analyze the quantitative data.

In the satisfaction/acceptability measure, free comments will be analyzed using thematic analysis.

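### Program-satisfaction ratings are assigned to the primary mixed model, but they are collected once, at T9, before the wait-list arm has used SPARX, so that model cannot be fitted to them

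*Protocol article*

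**What the plan says.** All references are to the protocol article.

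- **Model.** Statistical Analyses specifies a linear mixed model for PHQ-9 with assignment and time (T1 to T9), "with interaction of the assignment and time as fixed-effect variables and participants as a random-effects variable".
- **Extension to secondary outcomes.** The same section then says: "Secondary outcomes (outcome measures, process measures, and evaluation of the program) will be analyzed in the same way as the primary outcome". Program evaluation is named, so the ratings are not swept in by accident of wording. The section gives the free-text comments their own thematic analysis, but gives the numeric ratings no other rule. It sets a .05 significance threshold for every analysis.
- **Status.** The text closing the section on the DLSS reads: "The final secondary outcome will be a measure of the satisfaction and acceptability of the intervention".
- **Timing.** In Table 1 (Measures), the row "Satisfaction and acceptability" has a single tick, under T9. The footnote defines this as "T9: assessment at 1-month follow-up".
- **Respondents.** "All participants will be asked to rate four statements related to the perceived helpfulness, satisfaction with use, and the depth of understanding" of the content. The questions that follow ask how useful, how satisfying and how much fun the program was, each from 0 to 10.
- **Exposure of the wait-list arm.** Study Procedure says: "They will not be granted access to SPARX until all assessments have been completed". Wait-List Control gives the wait as 11 weeks, ending after the 1-month follow-up.

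**The concern.** A repeated-measures model has been assigned to an outcome that is not repeated, and a between-arm comparison to an outcome that only one arm is in a position to report. An analyst following the text would have to improvise. Dropping the time terms leaves a contrast between users and non-users of the thing being rated, tested at .05. Any other analysis would be chosen after the ratings are in hand.

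The Abstract lists satisfaction with the program first among the secondary outcomes, and the Discussion looks ahead to implementing such programs in student health services. The ratings are therefore likely to be reported and read.

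A smaller mismatch sits beside this. Depth of understanding is named in the outcome description and again in Results, but none of the listed questions asks about it.

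**Working it through.** **Sample size, for the counts used below.** Sample Size gives 90 evaluable participants for an effect size of 0.60, two-sided alpha .05 and power 0.80. The two-sample t-test calculation gives 44.6 per arm, rounded up to 45, so 2 × 45 = 90 with power 0.804. Allowing for 10% dropout, 90 / 0.90 = 100, or 50 per arm. The plan's figures reproduce and are not in dispute.

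**Fixed effects.** With two arms and V visits, the model has 2 × V columns: intercept, arm, V − 1 time terms and V − 1 interaction terms. The rank of the design matrix, built with 50 per arm on the Table 1 schedule, shows how many are identified.

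| Outcome and schedule | Columns | Rank | Observations per person |
|---|---|---|---|
| PHQ-9, T1 to T9 | 2 × 9 = 18 | 18 | 9 |
| Scales at T1, T8, T9 | 2 × 3 = 6 | 6 | 3 |
| Satisfaction, T9, both arms, nine time levels | 18 | 2 | 1 |
| Satisfaction, T9, both arms, three time levels | 6 | 2 | 1 |
| Satisfaction, T9, SPARX arm only, three time levels | 6 | 1 | 1 |

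With V = 1, time has V − 1 = 0 degrees of freedom, and assignment-by-time has (2 − 1) × (V − 1) = 0. All that is identified is one mean per arm. If only SPARX users answer, the arm effect goes too.

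**Random effect.** With one rating per person, the variance of a rating is the sum of the participant variance and the residual variance. Only the sum can be estimated, so the participant effect cannot be fitted.

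**The remaining contrast.** The difference between the two arm means at T9 can be computed. Setting Table 1 beside Study Procedure and Wait-List Control shows what it would be: one arm has been offered the seven modules, and the other has not yet been given access. If every wait-list participant answers, the number of such respondents is between 50 × 0.90 = 45 (planned dropout applied) and 50 (none).

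**The items.** The listed questions contain three 0-10 ratings (useful, satisfied, fun) and free-text requests (useful components, pros and cons). None concerns understanding of the content.

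**The case against.** **It corrects itself.** Satisfaction is absent from the five secondary objectives, carries no hypothesis and plays no part in the sample size. Any analyst would see that time has one level and drop it, and no data would be lost. This stands as an argument about severity. It does not make the sentence right, because what remains after dropping time is the uninterpretable arm contrast.

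**The wait-list arm may not be meant to answer at T9.** The items are worded for users, and Wait-List Control offers that arm SPARX afterwards on the same terms. A reader might infer that half of the 100 participants will certainly rate a program they have never used. The documents do not establish that: the wording about all participants is poorly reconciled with the access rule, and the planned dropout lowers the count. Equally, no later collection point is written. Table 1 gives T9 only, and Study Procedure has the wait-list arm complete its assessments at the same times as the treatment arm. The 45 to 50 is therefore what a literal reading gives, not an established number.

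**A fourth rating may not be missing.** A reader might infer that one of four promised ratings was left out. Four quoted prompts are printed, one of them free text, and the reference to four statements can be matched to those. The slip may be only in calling all four rated. The lack of a question on understanding stands on either count.

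**Conclusion.** The point holds in limited form. As written, the plan for the numeric program ratings cannot be carried out: 2 of 18 fixed-effect columns are identified (2 of 6 with three time levels), the interaction has 0 degrees of freedom, and the participant variance is not identifiable. The one contrast that can be computed, between arms at T9, has no useful meaning because the wait-list arm has not had the program. This rests on Table 1's single tick and on the access rule in Study Procedure and Wait-List Control. It does not rest on any assumed effect or variance.

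A reader might infer that the secondary analyses in general, or the trial's main conclusion, are compromised. They are not. PHQ-9 and the scales measured at T1, T8 and T9 give full-rank designs, and the free-text comments have their own method. The severity is minor to should-fix.

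**What to change.** 1. In Statistical Analyses, remove program evaluation from the sentence that applies the primary model to secondary outcomes.
2. In the outcome description at the end of the DLSS section, restrict the T9 ratings to the SPARX arm. Report each as a mean with a 95% confidence interval and the number answering out of the number randomized to SPARX, with no between-arm P value.
3. In that description and in Results, state what is collected: three 0-10 ratings (useful, satisfied, fun) plus free text, with no claim to measure depth of understanding.

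These are wording changes and need no new data. The only loss is a between-arm P value that had no valid meaning. Adding a question on understanding, or a later form for the wait-list arm, is not needed to correct the error and would cost more. Results reports 60 people already recruited and 24 in treatment, and Ethics lists three institutional approvals. A changed form could therefore need amendments and could leave early participants without the new item.

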### Objectives

The primary objective of this trial is to examine whether SPARX improves depressive symptoms in Japanese university students who present mild-to-moderate symptoms. We hypothesize that SPARX will be more effective for improving depressive symptoms than a wait-list condition. In the systematic review of trials of internet-based and computer-delivered interventions for university students [14], although half of the included trials used an inactive control group (wait-list or no treatment), the other half used an active control (eg, attention training or providing educational information on anxiety and depressive disorders). This will be the first clinical trial of SPARX for university students in Japan. Therefore, we will examine the difference between a SPARX group and a wait-list control group.

The secondary objectives are to determine whether SPARX delivered to Japanese students with mild-to-moderate depressive symptoms leads to (1) enhanced positive mood and reduced negative mood, (2) improved satisfaction with life, (3) improved health-related quality of life, (4) reduced depressive rumination, and (5) improved coping skills.

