### Sample Size

A meta-analysis of RCTs examining the effects of CBT in comparison to wait-list on depression in university students showed an effect size of 1.13 [34]. However, the effect sizes were smaller (0.56 [35] and 0.64 [36]) for studies in adults compared to those of internet-based and other computerized psychological treatments with wait lists. A meta-analysis of RCTs to examine the effectiveness of game-based digital interventions showed an overall effect size of 0.66 (against a wait-list control condition), 0.47 (with a target population of adolescent users), and 0.41 (type of game: psychoeducation and training, including the SPARX study) [22]. Additionally, a meta-analysis of RCTs to examine the effectiveness of technology-delivered interventions for depression and anxiety in children and adolescents showed an effect size of 0.45 compared to the wait-list group [37]. Considering these findings, we assumed a similar effect size (0.60) to that of internet-based and other computerized psychological treatments or game-based digital interventions against wait-list [22,35,36] for the reduction of primary outcomes assessed using Patient Health Questionnaire-9 (PHQ-9).

A power analysis showed that a target sample size of 90 was needed to detect an effect size of 0.60 with alpha=.05 and a power of 0.80 for a two-tailed test. Considering an anticipated 10% dropout [38], we will aim to recruit at least 100 (50 per group) participants to test the primary hypothesis of this study.

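### The P<.05 rule covers every secondary scale without order, adjustment or supportive status, so a false-positive secondary result is likelier than the nominal level suggests

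*Protocol article*

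**What the plan says.** The Objectives section lists five secondary aims (mood, life satisfaction, health-related quality of life, rumination and coping), introduced by "The secondary objectives are to determine whether SPARX delivered to Japanese students with mild-to-moderate depressive symptoms leads to" an improvement in each.

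The Measures section and Table 1 assign these aims to POMS-2, SWLS, the EuroQol instrument, the rumination scale and Brief COPE, each measured at T1, T8 and T9. A sixth instrument at the same times, the DLSS, also stands under the secondary heading: "This is a self-reported questionnaire for assessing daily life stressors for undergraduates". Satisfaction ratings at T9 complete the list: "The final secondary outcome will be a measure of the satisfaction and acceptability of the intervention".

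The Statistical Analyses section gives the model and the threshold. On the model: "Secondary outcomes (outcome measures, process measures, and evaluation of the program) will be analyzed in the same way as the primary outcome". On the threshold: "For all analyses, *P*<.05 will be inferred as statistically significant". It does not rank the secondary outcomes, make them conditional on the PHQ-9 result, adjust their P values or call them supportive or exploratory.

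**The concern.** The article is not silent on the threshold. It states a rule and extends it to every analysis. Applied as written, any one of five or six scales may be called statistically significant on its own P value, whatever the PHQ-9 shows. The secondary aims are worded as questions the trial will settle, and all the scales are self-reported by participants who know whether they are using SPARX or waiting.

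At stake is how a mixed result would be read. With a null PHQ-9 result and one secondary scale below .05, the stated rule lets the report describe an effect of SPARX on that scale in the same terms as a primary finding. A reader would not know how often chance alone produces such a pattern.

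**Working it through.** **The plan's own use of alpha.** The Sample Size section powers the trial for an "effect size of 0.60 with alpha=.05 and a power of 0.80 for a two-tailed test". By the normal approximation, n per arm = 2 × (1.96 + 0.84)² / 0.60² = 43.6, so 44 per arm or 88 in total. The t-test version gives 44.6, so 45 per arm or 90 in total, with power 0.804. Allowing for 10% dropout, 90 / 0.90 = 100. The stated 90 and 100 are reproduced. They belong to one PHQ-9 test; no error rate is stated for the secondary outcomes as a family.

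**Inputs for the secondary family.**
- Per-test level: 0.05, from Statistical Analyses. Taken as two-sided, as in Sample Size.
- Number of scales k: 5 (those matching the objectives) or 6 (adding DLSS). Satisfaction items are not counted.
- One test per scale. This is a simplification, because the model has two post-baseline times.
- Between-scale correlation ρ of the test statistics, each oriented so that positive means benefit. It is not given; assumed 0 to 0.8.

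**Independent tests.**
- Either direction: 1 − 0.95^k = 0.226 (k = 5) and 0.265 (k = 6).
- Benefit only: 1 − 0.975^k = 0.119 (k = 5) and 0.141 (k = 6).

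**Correlated tests.** Take Z_j = √ρ·U + √(1−ρ)·E_j, with U and E_j independent standard normal, and no true effects. Count the share of 2,000,000 simulated trials in which any |Z_j| > 1.96 (either direction) or any Z_j > 1.96 (benefit only).

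| ρ | k = 5, either | k = 5, benefit | k = 6, either | k = 6, benefit |
|---|---|---|---|---|
| 0 | 0.226 | 0.119 | 0.265 | 0.141 |
| 0.3 | 0.209 | 0.105 | 0.241 | 0.122 |
| 0.5 | 0.183 | 0.091 | 0.207 | 0.103 |
| 0.8 | 0.127 | 0.064 | 0.139 | 0.069 |

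A single two-sided test at .05 has a 0.025 chance of falsely showing benefit. At ρ = 0.5 the family has 0.091 / 0.025 = 3.6 times (k = 5) or 0.103 / 0.025 = 4.1 times (k = 6) that chance.

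**Sensitivity to the form of the test.** A 2-df assignment-by-time test per scale, the closest match to the stated model, gives almost the same either-direction rates at ρ = 0.5: 0.186 (k = 5) and 0.211 (k = 6). If T8 and T9 were each read at .05, with an assumed within-scale correlation of 0.6, those rates would be 0.302 and 0.337. The article does not say that the two times will be read separately, so these last figures show only the direction of change.

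**The case against.** The strongest reply has four parts.

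1. *The article promises no familywise control over the secondary outcomes.* This stands. A per-test rule delivers its per-test error, and no stated figure is contradicted. A reader might infer that a 5% family rate has been breached; no such target is set.

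2. *The article does separate primary from secondary.* This also stands. The PHQ-9 is named as primary, the explicit hypothesis concerns depressive symptoms only, and the sample size serves that hypothesis alone. What is absent is a statement of what a secondary P value may be used for. The shared threshold then treats both tiers alike.

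3. *Selective emphasis is already limited.* In part. The trial is registered, scales and times are published in advance, POMS-2 is reduced to one score, subgroup analyses are ruled out, and publication is promised whatever the outcome. None of these controls the error rate, but it would be wrong to say that no safeguard exists. Nor does the article say that a secondary scale alone would support an efficacy claim; its conclusion concerns the treatment of depression.

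4. *Multiplicity for secondary outcomes is commonly left to the analysis plan.* True of silence, but here a threshold for all analyses is stated. A later plan that made secondary results exploratory or gated would have to depart from that sentence.

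The size of the family is also open to argument. DLSS measures stressors and matches none of the five objectives, so five is the more natural count and six the upper one.

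**Conclusion.** The point holds as a low-cost improvement to the secondary analysis. The stated rule lets any secondary scale be declared significant on its own. Under no true effects and one two-sided test per scale, it gives a 0.13 to 0.27 chance of at least one false positive in either direction, and 0.06 to 0.14 for a false claim of benefit. At an assumed correlation of 0.5 these are 0.18 to 0.21 and 0.09 to 0.10. The ranges rest on five or six scales and correlations from 0 to 0.8, which are assumptions of this check and not figures from the article.

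Two stronger readings should be resisted. A reader might take the figure of about one in five as the chance of wrongly reporting that SPARX helped on some scale. It counts results in either direction, and the benefit figure is about half. A reader might also infer that the main conclusion is weakened, but the type I error of the single PHQ-9 test is untouched by this point.

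**What to change.** Limit the significance rule to the primary analysis and give the secondary outcomes a stated role. Suggested wording:

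> The primary PHQ-9 test uses two-sided P<.05. Secondary outcomes are supportive. They will be reported as estimates with 95% confidence intervals and nominal P values, and no claim of efficacy will rest on them.

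The secondary objectives should be phrased to match in the report.

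If formal secondary claims are wanted, one option is to test the five objective scales only after a significant primary result, with one pre-chosen contrast each and Holm adjustment at two-sided .05 (the smallest P value is compared with 0.05 / 5 = 0.01). This is a trade-off, not a requirement: each scale loses some power, and the trial was not sized for these outcomes.

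The main change costs one or two sentences and needs no new data or participants. Its downside is that a nominally significant secondary result can no longer be presented as a confirmed effect.
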